### Sample Size

The sample size was calculated using the PASS 2021 software after conducting a pilot trial. In the pilot trial, 88% (23/26) of the participants in the pay-it-forward group and 12% (3/26) of the participants in the standard-of-care group received the pneumonia vaccine. On the basis of the pilot trial results, we initially calculated the sample size to be 16. However, this sample size was determined to be too small to detect the desired effect size for the trial. To address this, we reviewed previous data on vaccination rates and estimated the expected difference in rates between the 2 groups based on prior experience. An earlier review indicated that the vaccination coverage of PPSV-23 among older adults in China ranged from approximately 1.23% to 42.10% [16]. Our previous pilot study showed that the pay-it-forward intervention increased influenza vaccination coverage in older adults by approximately 30% [23]. Considering these, we estimated a PPSV-23 vaccination coverage of 10% in older adults, and projected that the pay-it-forward intervention would increase this by 20%. The power of the test was set as 90% using a 2-sided test with a significance level of.05. The minimum sample size was calculated to be 158. After accounting for a 20% dropout rate, the minimum sample size required was adjusted to 198. The minimum sample size was further increased to 204 to accommodate the block-randomized design. Consequently, at least 204 participants were required for the trial.

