The uptake of PPSV-23 will be verified using the immunization program’s information management system. Separate questionnaires will be administered to participants in the standard-of-care and pay-it-forward groups. Quality control questions have been included to ensure the accuracy of questionnaire completion. Two similar questions will be included in different sections of the questionnaire to assess the consistency of responses: (1) Does vaccination with PPSV-23 reduce hospitalization and deaths? and (2) Vaccination with PPSV-23 reduces hospitalization and death. If participants respond differently to these 2 similar questions, the questionnaire will be considered invalid, and they will be asked to complete it again. Once participants are enrolled, personally identifiable information and survey data will be entered into an electronic Microsoft Excel form. The form will be password-protected by the study designer, and only the study designer and the researcher responsible for data analysis will have access to it. A data safety and oversight committee will be established, comprising 2 clinicians, an epidemiologist and statistician, and a representative of the medical ethics committee, who will operate independently of the research team. The data safety and oversight committee will review the process of the study, data collection, data management, and analysis. Each participant will be assisted by a CHW in completing the survey. For older adults who do not have a smartphone, the survey will be completed using an electronic device provided by the research program, and the CHW will guide them through the QR code scanning and submission process.

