### Outcome Measures

The primary outcome of this study will be the uptake of PPSV-23 in each arm, assessed 1 month after the intervention using administrative records. The secondary outcomes will include: (1) vaccine confidence, measured by 4 survey statements related to perceptions of the importance, safety, and efficacy of vaccination, as well as vaccine management; (2) influenza vaccination, defined as participants receiving the influenza vaccine after enrollment in the study, verified through administrative records, with the cost of the vaccination borne by the participants; (3) cost per person vaccinated and cost-effectiveness; (4) vaccine knowledge between the 2 groups; (5) attitudes toward vaccination; (6) willingness to vaccinate; (7) gratitude, measured by the GQ-6 scale; (8) the rate of successful vaccine referral, defined as participants successfully recommending PPSV-23 to others in the community after participating in the study; and (9) incidence of adverse events or reactions to vaccination.

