#### Secondary Outcomes

The economic evaluation will be conducted from a health care provider’s perspective with a 1-year time horizon. Microcosting methods will be used to evaluate the implementation costs of both the standard-of-care and pay-it-forward intervention groups. Specifically, we will collect cost data, including personnel time, medical supplies, equipment use, and facility expenses. Material procurement costs will be calculated using primary sources, such as invoices, while project implementation costs will be based on researchers’ self-reported data. Health care personnel’s time costs will be estimated using the local government–published wage standards. A decision tree model will be developed using TreeAge Pro 2022 software (TreeAge Software, LLC), with vaccination uptake (defined as the number of vaccinated individuals per intervention arm) serving as the effectiveness measure for the pay-it-forward intervention. The intervention will be compared against standard-of-care (participants’ self-paid PPSV-23 vaccination) to estimate incremental costs and incremental cost-effectiveness ratios. Model robustness will be assessed through 1-way sensitivity analyses and probabilistic sensitivity analysis. Influenza vaccination rates and vaccine confidence will be compared between the pay-it-forward intervention group and the standard-of-care group using logistic regression analyses, adjusted for sociodemographic information. Other secondary outcomes will be summarized using descriptive statistics and compared between the 2 arms.

Participants with missing primary outcome data (ie, vaccination status) will be reviewed. A complete case analysis will be performed if the proportion of missing primary outcome data is low (<5%). If the missing data exceed this threshold, multiple imputation methods will be applied under the assumption that the data are missing at random, to account for potential bias. Sensitivity analyses will also be conducted to assess the robustness of the findings under different assumptions about the missing data. To address missing follow-up data, we will use the last observation carried forward method or a multiple imputation method for missing values for categorical and continuous variables.

The results of all logistic regression analyses will be reported as crude odds ratios and adjusted odds ratios, along with 95% CIs. All statistical tests will be 2-sided, with a significance level of *P*<.05.

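### LOCF is left open as an alternative to multiple imputation for missed questionnaires and can bias the week-2 and week-4 comparisons; registry look-up of uptake should be stated as independent of survey completion

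*Protocol article*

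**What the plan says.** The missing-data rules stand in the protocol article under Statistical Analysis, Secondary Outcomes.

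- **Follow-up data:** "we will use the last observation carried forward method or a multiple imputation method for missing values for categorical and continuous variables". The text does not say which method serves which variable, or what decides between them.
- **Primary outcome:** "Participants with missing primary outcome data (ie, vaccination status) will be reviewed". Then "A complete case analysis will be performed if the proportion of missing primary outcome data is low (<5" per cent). Above that threshold, "multiple imputation methods will be applied under the assumption that the data are missing at random, to account for potential bias".
- **Safeguard:** "Sensitivity analyses will also be conducted to assess the robustness of the findings under different assumptions about the missing data".

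Uptake itself does not come from the questionnaires. Outcome Measures says it is "assessed 1 month after the intervention using administrative records", and Data Collection and Management says "The uptake of PPSV-23 will be verified using the immunization program’s information management system". The latter section also has name and identification number recorded at enrollment. Table 2 shows knowledge, attitudes and gratitude in questionnaires A, B and C, but adverse events and recommendation to others in B and C only.

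**The concern.** LOCF assumes that a person who stops answering would have kept giving the last answer. It also treats the carried value as if it had been observed. Three features of this trial make that doubtful.

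1. Both Intervention subsections place questionnaire A after the leaflet and video. In the pay-it-forward arm it also follows the explanation of the subsidy, donations and postcards. Carrying A to week 4 puts an early post-exposure score in place of a later one.
2. Strengths and Limitations expects that the follow-up surveys may themselves improve knowledge somewhat. The protocol thus allows for the change over time that LOCF rules out.
3. For items asked only in B and C, LOCF has either a week-2 answer to carry or none at all.

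Enrollment and follow-up have ended and results are pending. An open choice between two methods could therefore be settled with the data in hand.

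The primary-outcome rule raises a smaller question. Uptake can in principle be looked up from the identification number without a survey. Yet no section says that survey non-responders are looked up, or how a person with no vaccination record is coded. Below 5% missing, the rule removes randomised participants from an analysis described as intention-to-treat.

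**Working it through.** **Inputs from Sample Size.** Rates 10% and 30% (10% plus 20 points), two-sided 0.05, power 90%, and "After accounting for a 20% dropout rate, the minimum sample size required was adjusted to 198".

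*The plan's own figures.* With unpooled variance, n per arm = (1.960 + 1.282)² × (0.10×0.90 + 0.30×0.70) / 0.20² = 78.8, so 79 per arm and 158 in total. Then 158/0.80 = 197.5, so 198. Both reproduce. The 20% is used below only to illustrate a share of missed questionnaires.

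**LOCF, mean difference.** Let D4 be the true week-4 arm difference and DA the difference at questionnaire A. Assume that a share d of each arm misses both follow-ups and otherwise resembles the rest:

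LOCF estimate = (1−d)·D4 + d·DA

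With d = 0.20:

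| DA | LOCF estimate | Error |
|---|---|---|
| 0 | 0.80·D4 | 20% too small |
| D4 | 1.00·D4 | none |
| 2·D4 | 1.20·D4 | 20% too large |

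The values of DA are assumptions. A participant who completed B carries B, not A, so for that person the week-2 difference replaces DA.

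**LOCF, unequal missingness.** Suppose no true effect, equal arms at the carried visit, a common change g over time, and 10% missing in one arm against 30% in the other. The LOCF mean changes are 0.90g and 0.70g, a false difference of 0.20g. With equal missingness it is zero.

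**LOCF, precision.** If 20% of values are carried but counted as observed, and the standard error scales with 1/√n, the reported value is √0.80 = 0.894 of the one that the observed data support, or about 11% too small.

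**Items asked only in B and C.** Vaccination is by appointment after enrollment, so a week-2 answer may precede it. Carried forward, it could record no reaction for someone vaccinated later. Data Collection and Management limits the adverse-event item to vaccinated participants. If that is applied strictly at week 2, such a person has no answer to carry. A person who misses both B and C also has none.

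**Primary outcome, complete case at the 5% limit.** Assume that 5% of each arm lack status and that all of them are unvaccinated:

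- Difference: 0.30/0.95 − 0.10/0.95 = 31.6% − 10.5% = 21.1 points, against 20.
- Odds ratio: (0.30/0.65)/(0.10/0.85) = 3.92, against (0.30/0.70)/(0.10/0.90) = 3.86.

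Outer bounds with 10 of 204 missing (4.9%), 102 per arm, and 31 against 10 vaccinated (20.6 points):

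- All 10 missing vaccinated and in the pay-it-forward arm: 21/92 − 10/102 = 13.0 points.
- All 10 missing vaccinated and in the standard-of-care arm: 31/102 − 0/92 = 30.4 points.

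These are extremes, not expectations.

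**The threshold.** Complete case applies below 5% and imputation above it. Exactly 5%, which is 11 of the 220 enrolled, falls under neither.

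**The case against.** **On the questionnaires.** The text offers multiple imputation as well as LOCF, so bias is possible rather than certain. The allocation of methods to variables is commonly left to an analysis plan, which is not shown. These are secondary outcomes, and most are only to be described and compared. Where nothing can be carried, imputation remains available. All of this stands, and it limits the size of the point. It does not make LOCF suitable, and the protocol itself names LOCF as an acceptable main method.

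A reader might infer that LOCF freezes an immediate peak and so exaggerates the effect. The documents do not show that. They say only that A follows the video, and their remark on knowledge points to a possible later rise.

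**On uptake.** The rule covers only participants whose vaccination status is missing, after a review, and sensitivity analyses are planned. It does not say that survey dropouts are excluded or imputed. Full look-up is a reasonable inference but is not stated: participants may opt out at any time, and registry coverage is not described. A fallback for true gaps is normal.

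A reader might take the 20% dropout allowance as the share without vaccination status. If all of those were unvaccinated, 30% against 10% would become 37.5% against 12.5%, or 25 points instead of 20. The documents do not support this. The 20% inflates the sample size and does not forecast missing registry entries, and exclusion is allowed only below 5%. Likewise, setting about 90% power at 79 per arm against about 97% at 110 per arm shows a sample size with some reserve. It does not show a loss caused by the missing-data rule.

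**Conclusion.** The point holds for the questionnaire outcomes. LOCF is allowed and the choice is open. LOCF can bias the week-2 and week-4 comparisons and understate their standard errors. At 20% missing both follow-ups, the error runs from −20% to +20% of D4 as DA goes from 0 to twice D4. The direction is not established, and the figure shrinks with less missingness or where B was completed.

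For the primary outcome the point is one of clarity. The plan does not tie look-up to survey completion, but neither does it separate them or say how no record is coded. The 5% switch adds little. The expected effect is about 1 point at the 5% limit if the missing are unvaccinated and equally frequent in both arms. Larger shifts need missingness concentrated in one arm with one status, and nothing in the documents suggests that.

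**What to change.** Record the following in an amendment or a dated analysis plan before arm codes are revealed to the analysts.

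1. Delete LOCF and name one method per type of outcome. For scores measured at A, B and C, a mixed model with arm, time and arm-by-time would serve. Questionnaire A should enter as a measured time point, not as a pre-intervention baseline. For items asked only at follow-up, use multiple imputation within arm.
2. State that uptake is looked up for every randomised participant regardless of survey completion, and that no record within the window counts as not vaccinated.
3. Replace the 5% complete-case switch: keep multiple imputation and the planned sensitivity analyses only for records that cannot be accessed, for example after consent is withdrawn.

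The cost is analysis wording and slightly more programming, with no new data from participants. The drawback is that vaccinations given outside the registry count as no.

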### Ethical Considerations

The study was approved by the medical ethics committee of Guangxi Medical University (Ethics No. KY0261, 2023) in accordance with the Declaration of Helsinki. All participants will be required to provide written informed consent before participating in the study. Participants have the option to opt out at any time. All collected data will be anonymized and deidentified to ensure privacy and confidentiality protection. Informed consent covers secondary analysis without additional consent. Participants who complete all three questionnaires will receive compensation of 100 RMB (US $13.99).

## Results

Participant recruitment took place from January 2024 to September 2024. We enrolled 220 participants. Final results are anticipated in June 2026.

## Discussion

### Expected Outcomes

The purpose of this study is to evaluate the effectiveness of a pay-it-forward intervention in promoting PPSV-23 vaccination among older adults aged ≥60 years. The results will inform the future development of pneumococcal vaccination interventions for older adults and contribute to the development of more cost-effective and sustainable public health policies.

The prevalence of pneumococcal diseases among older adults in China remains high, yet the coverage rate of PPSV-23 (ie, 1.23%-42.10%) [16] is significantly lower than that in high-income countries (52%-75%) [32-34]. Free pneumococcal vaccinations have been implemented for community residents in some high-income cities, such as Beijing, Shanghai, and Guangzhou [35]. However, in areas with limited health resources, the government faces challenges in providing free pneumococcal vaccines to community dwellers because of insufficient funding. Therefore, it is imperative to implement practical and feasible interventions to promote vaccination uptake. Previous studies have demonstrated the effectiveness of the pay-it-forward intervention targeting influenza vaccination or testing for gonorrhea and chlamydia in high-income areas of China [20,23]. However, the efficacy of this intervention in resource-limited regions has not yet been studied. This trial will be the first to assess the effectiveness of a pay-it-forward intervention in promoting the uptake of PPSV-23 for older adults in low-income areas in China. In addition, a self-designed questionnaire will be used to determine the differences in cost-effectiveness, knowledge, attitudes, willingness to vaccinate, and perceptions of gratitude between the pay-it-forward and standard-of-care groups. This study may provide insights into the development and optimization of pneumonia immunization strategies in regions with limited resources.

We anticipate that this study will provide evidence supporting the feasibility of the “pay-it-forward” intervention in vaccine services and offer valuable insight for evidence-based practice in future vaccine programs. Currently, the PPSV-23 is not included in China’s National Immunization Program, requiring individuals to bear the cost of vaccination, which limits the uptake of the PPSV-23 in resource-limited areas. The “pay-it-forward” approach may promote vaccination in these areas. In the absence of government funding for vaccination, the pay-it-forward model may effectively pool small donations to support more individuals in accessing pneumonia vaccine services, which is of significant importance for improving vaccination coverage in areas with relatively insufficient health resources. Moreover, the “pay-it-forward” strategy has demonstrated high cost-effectiveness in promoting influenza vaccination [36]. By evaluating cost-effectiveness, this study may inform decision-making regarding expansion strategies, enabling stakeholders to make informed resource allocation decisions.

Previous studies have shown that implementing free vaccination policies has enhanced the coverage of PPSV-23 [37,38]. However, implementing free vaccination strategies in low-income areas with limited health resources remains challenging. Prior randomized controlled trials have explored educational information interventions to increase vaccination uptake [39,40]. However, immediate improvements in knowledge and risk perception have not immediately led to changes in vaccination behavior. Vaccine price, vaccine accessibility, and vaccine confidence are additional factors influencing vaccination behavior. This study is the first to use a randomized controlled trial to evaluate the effectiveness of the pay-it-forward intervention for PPSV-23 vaccination. Through community engagement, vaccination subsidies, and public education, the intervention aims to enhance knowledge about the vaccine, bolster confidence in its safety and efficacy, attract financial contributions, and ultimately promote vaccination.

### Strengths and Limitations

This study uses a randomized controlled trial to evaluate the effectiveness of the innovative pay-it-forward intervention in improving PPSV-23 vaccination rates among older adults, while comprehensively assessing its multidimensional impacts on vaccination-related cognition, behaviors, and economic outcomes. By validating this novel approach that integrates economic incentives with social mobilization, the findings will provide evidence-based insights for developing cost-effective vaccination promotion strategies, particularly facilitating the optimization of pneumococcal vaccination policies in low- and middle-income regions.

Some limitations exist in this study. First, the questionnaires rely on self-reports, which may introduce biases in specific responses. However, this should not impact the vaccination rate, as it will be verified through the vaccination information management system of CHCs. Second, the sample size for exploring factors associated with willingness to vaccinate is insufficient, and additional cross-sectional studies with rigorous sampling and a larger sample size are necessary to determine these factors. Third, conducting 2 follow-up surveys within a month may improve the participants’ knowledge of vaccines to some extent, but it may not be sufficient to change their attitudes and behaviors toward the PPSV-23 quickly. Finally, there is a possibility of cross-contamination in this study. We implemented contamination control measures: (1) prohibiting the sharing of intervention details; (2) using group-specific materials and separate discussion spaces; and (3) applying both intention-to-treat and per-protocol analyses to assess potential contamination effects.

### Future Directions

Future research should incorporate a free vaccination group to better isolate and quantify the specific effects of the pay-it-forward intervention. This innovative model is expected to facilitate the uptake of public health services, and additional implementation studies (eg, disease screening) could be conducted to assess its feasibility in different settings.

### Dissemination Plan

The trial results will be disseminated to the study participants, health care professionals, public health authorities, and the scientific community. The findings will be published in peer-reviewed journals, presented at conferences, and reported in trial registries, such as the Chinese Clinical Trial Registry (ChiCTR). Briefings will be provided to participating CHCs, and lay summaries may be shared with the public via digital platforms (eg, WeChat).

### Conclusions

In summary, this study aims to assess the effectiveness and cost-effectiveness of the “pay-it-forward” intervention in the vaccination with PPSV-23 among older adults. This innovative payment model may offer a new approach to enhance vaccination uptake in resource-limited regions, ensuring access to vaccination services, especially in settings with limited health care resources. In addition, the pay-it-forward strategy may act as a transitional step toward gradually shifting from individual payment-based vaccination policies to publicly funded ones.

